## Methods

### Objectives

The VITALE study is designed to evaluate whether high doses of cholecalciferol in RTRs with vitamin D insufficiency has beneficial effects upon the late post-transplant outcome compared with low-dose supplementation. As a primary outcome, we will evaluate the impact of cholecalciferol on a composite endpoint including *de novo* DM (fasting glycaemia >7 mmol/l or glycaemia >11 mmol/l), major cardiovascular events (acute coronary heart disease, acute heart failure, lower-extremity arterial disease, cerebrovascular disease), *de novo* cancer, and patient death. Secondary objectives will compare the effects of high-dose versus low-dose cholecalciferol on BP and on BP control (number and dosage of antihypertensive drugs), echocardiography findings, infections (including cytomegalovirus, *Pneumocystis*, nocardial infection, cryptococcal infection, aspergillosis), acute rejection episodes, renal allograft function including Modification of the Diet in Renal Disease (MDRD)-v4 estimated glomerular filtration rate (eGFR) [88], proteinuria and graft survival, and mineral metabolism biologically (serum calcium, phosphate, 25OHD and PTH) and clinically (graft nephrolithiasis, bone mineral density, measured body weight, and incidence of fractures) relevant parameters.

We have noted that, according to the published literature, some vitamin D experts especially involved in the cardiovascular field consider that optimal 25OHD concentration for cardiovascular health probably lies within a narrow range of 30 to 40 ng/ml [89, 90]. We took this advice into account, and one of the main objectives of our VITALE trial is thus to evaluate whether our treatment scheme, which probably will increase the 25OHD concentration above 40 ng/ml in a significant percentage of patients, is safe, especially in terms of cardiovascular health.

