### Study population and sample size

The study sample will consist of 640 RTRs found to be lacking sufficient vitamin D (25OHD <30 ng/ml) 12 to 48 months post-transplantation with 320 subjects in each study group. Inclusion and exclusion criteria are detailed in the Appendix. The sample size calculation was performed according to the following assumptions: The principal criteria will be the occurrence of one of the events of the composite endpoint including *de novo* DM, major cardiovascular events, *de novo* cancer, and patient death. Over a 2-year follow-up period, we estimate, according to previous reports in the literature, that the incidence of a first event of the composite endpoint will be around 22% in our population (6% for *de novo* T2DM [91, 92], 6% for major cardiovascular events [93–95], 7% for *de novo* cancers [15, 96], and 3% for patient death). This 22% global estimated incidence does not take into account the fact that some patients may experience several events of the composite endpoint during the follow-up period. According to the results of the numerous observational studies showing an inverse association between 25OHD concentrations and various clinical events and to the results of the few interventional trials showing effects of high-dose vitamin D supplementation on these events (detailed above),we estimate that the overall decrease in the incidence risk of a first event of the composite endpoint will be around 40% in the high-dose group compared with the low-dose group (33% decrease for *de novo* DM, 40% decrease for major cardiovascular events and 50% decrease for *de novo* cancer). Thus, to demonstrate the reduction in the incidence of a first event of the composite endpoint from 22% in the low-dose group to 13% in the high-dose group, with a 90% power and 5% α risk error, 582 RTRs (291 in each group) will be required. Taking into account that 10% of patients will not be evaluable, a total of 640 RTRs will be required. The inclusion of a total of 480 RTRs would allow us to test the same hypothesis with a power of 80%.

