All events occurring during the 2 years of follow-up will be recorded. The principal criteria (occurrence of the first event constituting the composite endpoint) will be compared between the two groups using the Cox model that takes into account the stratification by the centre. Secondary criteria will be compared using tests corresponding to the nature of the variable: *χ*^2^ or Fisher’s exact test for qualitative variables, parametric or non-parametric variance analysis for quantitative variables, and log-rank or Gray’s test for time to event. The secondary parameters that will be analysed are the following: the incidence of each of the events constituting the composite primary endpoint; BP measurement, and number, drug classes and doses of antihypertensive drugs necessary to reach normal BP; preventive coronary revascularisation; evolution of the left ventricular ejection fractions and of the left ventricular wall thickness assessed by transthoracic echocardiography; vitamin D insufficiency correction; evolution of the fasting urinary calcium/creatinine ratio and of serum calcium, phosphate, and PTH concentrations; bone fracture incidence; changes in body height; changes in bone mineral density at the lumbar spine and femoral neck; incidence of infectious episodes and type of infection; incidence of treated acute rejection episodes; evolution of MDRD eGFR, of urinary protein/creatinine ratio, and of urinary microalbuminuria/creatinine ratio; graft survival; evolution of HbA1C in the absence of DM; evolution of HbA1C and of anti-diabetic treatments in cases of *de novo* DM; or incidence of cholecalciferol-related side effects (hypercalcaemia, calcic nephrolithiasis and other spontaneously reported side effects). Adjustment for multiple testing will be performed using the Hochberg procedure for the components of the primary criteria. We will also describe in detail each adverse event (AE) that occurs during the study, and we will report the overall rate of occurrence of AE, the rate of withdrawal from the study due to an AE, the overall rate of patients with at least one clinically significant laboratory abnormality, the rate of AEs attributable to treatment (possible or probable relationship), and the rate of serious AEs. The percentage of patients with each of the AEs associated with cholecalciferol and the intensity of these AEs will be specified.

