For our study, we have chosen a composite criterion for efficacy. The main advantages supporting this choice are that it increases statistical efficiency because of a higher event rate, which reduces sample size requirement. In addition, it helps investigators avoid an arbitrary choice between several important outcomes that refer to the same disease process. Composite outcomes can be misleading when treatment effects vary across components with very different clinical importance. In our study, the rate of each event except for death is of similar magnitude. Moreover, we hypothesize that the rate reduction of each event composing the endpoint will be between 30% and 50%, giving a mean reduction of 40% overall. We also hypothesize that the drug will not affect death, but death is being included in the composite endpoint because it is a competing risk with major cardiovascular events. In order to limit misleading interpretation, we will clearly present data for all components and discuss the role of each in the total reduction of the composite event rate.

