### Conclusion and perspectives

In addition to its classic effects on bone and mineral metabolism, vitamin D displays a wide spectrum of potential non-classic effects that are especially relevant for the care of RTRs. These pleiotropic effects have been documented in observational and experimental studies or small intervention trials, which most often evaluated intermediate parameters. The time has now come for large placebo-controlled trials in RTRs, using larger dosages of vitamin D than the current recommended intakes, and targeting clinical endpoints. The VITALE study has been designed to demonstrate that high doses of vitamin D can reduce the risk of extra-osseous diseases without inducing AEs, and also aims to determine the necessary levels of 25OHD to achieve these effects. Furthermore, the RTR population may give interesting clues to the effects of vitamin D in the general population, as cardiovascular, diabetes mellitus, and cancer complications are much more frequent in the former than in the latter.

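### The article says the trial is designed to demonstrate benefit without adverse events, but a difference test at a sample size set by efficacy cannot demonstrate that side effects are not increased

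*Protocol article*

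**What the plan says.** All references are to the protocol article.

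- **Conclusion and perspectives** states the aim as a demonstration: "The VITALE study has been designed to demonstrate that high doses of vitamin D can reduce the risk of extra-osseous diseases without inducing AEs".
- **Objectives** makes it one of the main objectives to evaluate whether the treatment scheme "is safe, especially in terms of cardiovascular health".
- **Statistical analysis** gives the general rule: "Secondary criteria will be compared using tests corresponding to the nature of the variable". The tests named are chi-square or Fisher for qualitative variables, analysis of variance for quantitative ones, and log-rank or Gray for time to event. The list of secondary parameters ends with the "incidence of cholecalciferol-related side effects (hypercalcaemia, calcic nephrolithiasis and other spontaneously reported side effects").
- The same section promises descriptive reporting: overall, serious and attributable adverse-event rates, withdrawals due to adverse events, and clinically significant laboratory abnormalities. It adds: "The percentage of patients with each of the AEs associated with cholecalciferol and the intensity of these AEs will be specified".
- **Study population and sample size** derives the number of patients only from efficacy, "to demonstrate the reduction in the incidence of a first event of the composite endpoint from 22% in the low-dose group to 13" per cent in the high-dose group. That gives 291 per group evaluable and 320 per group randomized.

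The article states no side-effect rate, no margin and no excess to be excluded.

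**The concern.** A test of a difference is built to detect an excess. If it is not significant, the data may still fit a sizeable excess, above all when events are few. A statement that the high dose works "without inducing AEs" therefore needs either a margin or an upper limit on the excess, together with a sample size that makes that limit informative. The article pairs the demonstrative wording with neither.

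The article itself gives reasons for caution about high 25OHD levels and expects many patients to exceed 40 ng/ml. What is at stake is how a finding of no significant difference may be worded, and so the benefit/risk conclusion.

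**Working it through.** **The plan's own sample size.** Inputs: 22% versus 13%, 90% power, 5% alpha (sidedness not stated).

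- Hazard ratio = ln(0.87)/ln(0.78) = 0.560.
- Events (Schoenfeld) = 4(z_alpha + z_power)²/(ln HR)². With a one-sided 5% test this is 4(1.645 + 1.282)²/(ln 0.560)² = 102.2, so 103.
- Mean event probability = (0.22 + 0.13)/2 = 0.175, and 103/0.175 = 589, close to the stated 582. A two-sided test gives 126/0.175 = 720.
- 582 × 1.10 = 640.2, the stated total.

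Sidedness is a separate matter. For this point, what counts is that no side-effect rate or precision target enters the calculation.

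**Chance of missing a doubled side-effect risk.** Inputs: n = 291 per arm (evaluable) or 320 (randomized), both from the article; two-sided 5%; low-dose rate p assumed, because none is given. Miss rate = 1 − Σ Bin(i; n, p)·Bin(j; n, 2p), summed over outcomes with j > i and test p-value ≤ 0.05. In each range the lower figure is Pearson chi-square and the higher is Fisher.

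| Low vs high dose | Missed, 291 per arm | Missed, 320 per arm |
|---|---|---|
| 1% vs 2% | 85–92% | 83–90% |
| 2% vs 4% | 71–78% | 68–75% |
| 3% vs 6% | 58–65% | 55–62% |
| 5% vs 10% | 36–42% | 32–38% |
| 7% vs 14% | 20–25% | 17–20% |
| 10% vs 20% | 7–9% | 5–7% |

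By the normal approximation to the chi-square test, the 50% point lies at a low-dose rate of about 3.7% (291 per arm) or 3.4% (320 per arm). Fisher crosses a little higher.

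**What an interval would exclude.** Suppose both arms show the same observed rate p, with 291 per arm.

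- Upper 95% limit on the risk difference = 1.96·√(2p(1−p)/n). At p = 3%: 1.96·√(2 × 0.03 × 0.97/291) = 0.028.
- Upper 95% limit on the risk ratio = exp(1.96·√(2(1−p)/(np))). At p = 3%: exp(1.96·√(2 × 0.97/(291 × 0.03))) = 2.5.

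| Observed rate, both arms | Upper limit, difference | Upper limit, ratio |
|---|---|---|
| 1% | +1.6 points | 5.0 |
| 2% | +2.3 points | 3.1 |
| 3% | +2.8 points | 2.5 |
| 5% | +3.5 points | 2.0 |
| 10% | +4.9 points | 1.6 |

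**Number needed to exclude a doubling.** With margin = p, one-sided 2.5% and 80% power, n per arm = (1.96 + 0.842)²·2p(1−p)/p². This gives 1,555, 770, 508, 299 and 142 at p = 1%, 2%, 3%, 5% and 10%. The planned size is enough only from about 5% upwards.

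**The case against.** **No rule equates non-significance with safety.** A reader might infer that the investigators will treat a non-significant test as proof of safety. Nothing in the article says so. The Objectives section speaks of evaluating safety, and Risk analysis promises careful monitoring. The demonstrative sentence stands in the closing section, not among the analysis rules. This objection stands, and it limits the point to a claim that exceeds the design.

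**Intervals may be in the analysis plan.** This is fair. A superiority trial sized on efficacy, without a safety margin, is ordinary practice, and the absence of intervals from an article is not the finding. But intervals in an unseen plan would not make the concluding claim attainable at this sample size if the side effects are uncommon.

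**The rate is assumed.** A reader might infer that a doubling would usually be missed. The article does not support that without a condition: it gives no rate and does not say these side effects are rare. At 5% or more on low dose, a doubling is more often detected than missed.

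**Safety analysis is more than one test.** This is also correct. Descriptive rates are promised, and serum calcium and the urinary calcium/creatinine ratio are analysed as continuous measures, where power is not the difficulty. The point concerns side-effect incidence.

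**Death.** The Risk analysis statement "We also hypothesize that the drug will not affect death" might be read as a second safety claim. In context it is a planning assumption explaining why death is in the composite, and nothing here rests on it.

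**Conclusion.** The point holds in limited form. The article claims as a design property that the trial will demonstrate benefit without inducing adverse events. The only inferential comparison it states for cholecalciferol-related side effects is a difference test, and the sample size was fixed by efficacy alone. The design can estimate an excess of side effects; it cannot demonstrate that there is none.

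The practical size rests on an unknown low-dose rate. Below about 3.5%, a doubling would be missed more often than not; above that, detection improves quickly. At equal observed rates up to 5%, a risk ratio of about 2 or more would remain compatible with the data at 291 per arm. These figures assume two-sided 5% tests without multiplicity adjustment and simple binary incidence over follow-up.

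This is worth correcting because it governs what the trial may conclude. It is not a fault in the efficacy analysis.

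**What to change.** 1. In Statistical analysis, state that hypercalcaemia, calcic nephrolithiasis and other cholecalciferol-related side effects will each be reported as the high-minus-low risk difference with its 95% confidence interval.
2. Add that any safety conclusion will be worded as the largest excess excluded by the upper limit, and that a non-significant test will not be taken as absence of harm.
3. In Conclusion and perspectives, replace the claim of demonstrating benefit without inducing adverse events with wording that the trial will test for benefit and estimate the excess of adverse events. It would help to state what the planned size can exclude: about 1.6 to 3.5 percentage points if both arms show 1% to 5%.

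The cost is a few sentences and routine interval estimates from data already being collected, with no extra patients or visits. The only downside is a more modest safety claim.

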#### Patient follow-up

Five visits will be performed after randomization (Table 1). Vitamin D measurements after randomization will be centralized and performed at the end of the study. Given the absence of standardization and a reference method of vitamin D measurement when we submitted the VITALE trial to funders (early 2011), we planned to use the most referenced method (radioimmunoassay; Diasorin, Stillwater, MN, USA) [100]. Since then, a reference method has been accepted [101] and is now being used in an international program, the Vitamin D Standardization Program (VDSP), to harmonize vitamin D results [102]. We thus will use the assay (either immunoassay or commercial LC-MS-MS assay) that at the end of the VITALE study will provide results that are closest to the reference method [103]. This will allow us to determine with the best possible precision the optimal threshold of 25OHD level to prevent the occurrence of the clinical events constituting the principal criteria. In order to assess compliance, patients will be asked to return their empty vials at each follow-up visit.

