Some additional p*ost hoc* subgroup analyses will also be performed (according to, for example, baseline 25OHD levels, achieved 25OHD levels, VDR and vitamin D binding protein polymorphisms, and corticosteroid treatment, among others).

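### Achieved 25OHD arises after randomization, so the trial cannot determine a protective 25OHD threshold; HbA1c is likewise compared only in subsets formed after randomization

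*Protocol article*

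**What the plan says.** All references are to the protocol article.

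- **Subgroups.** The last paragraph of Statistical analysis says that post hoc "subgroup analyses will also be performed". Its examples include "baseline 25OHD levels, achieved 25OHD levels", next to genotype and corticosteroid treatment. Baseline and achieved levels are not distinguished in kind.
- **Threshold.** Patient follow-up states that "Vitamin D measurements after randomization will be centralized and performed at the end of the study". It then says that choosing the assay closest to the reference method will let the trial "determine with the best possible precision the optimal threshold of 25OHD level to prevent the occurrence of the clinical events" making up the primary criterion. Conclusion and perspectives says the study "also aims to determine the necessary levels of 25OHD to achieve these effects".
- **HbA1c.** Statistical analysis lists two HbA1c parameters among the secondary criteria to be compared between groups: "evolution of HbA1C in the absence of DM", and "evolution of HbA1C and of anti-diabetic treatments in cases of" de novo DM. No HbA1c comparison in all randomized patients is listed.
- **Sampling.** In Table 1, 25OHD after randomization is measured at months 3, 12 and 24, and HbA1c at inclusion and months 12 and 24.

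**The concern.** Randomization balances the arms as allocated. It does not balance patients grouped by something that happens afterwards. A high-dose patient and a low-dose patient who both reach 35 ng/ml got there by different routes. The low-dose patient may have more sun, better absorption or less catabolism; the high-dose patient may have poorer intake or worse health. A contrast between them mixes dose with those differences.

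The threshold aim has the same weakness. A more accurate assay reduces measurement error, but it removes neither confounding nor reverse causation. The protocol makes this argument itself: Anticancer properties of vitamin D says observational associations do not establish causality, and Effects of vitamin D on the cardiovascular system warns that low vitamin D may follow from disease. At stake is a 25OHD target reported with a randomized trial's authority but resting on the kind of evidence the trial was meant to improve on.

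The HbA1c comparisons raise a related, smaller issue. Diabetes is an exclusion criterion at entry, so both HbA1c subsets form only during follow-up, through an event that treatment is assumed to reduce.

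**Working it through.** The plan gives no figure on this point to reproduce. Step 1 is a reading of the text. Steps 2 to 4 only show the possible size of the problem.

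**1. What drives achieved 25OHD, according to the protocol**
- Allocated dose, and intake as checked by returned vials (Study intervention).
- Discontinuation for abnormal calcium or phosphate results (Study intervention).
- Immunosuppressive drugs, which increase 25OHD catabolism (Background). Corticosteroids and tacrolimus are also named as main causes of de novo diabetes (Anti-diabetic properties).
- Sun exposure, given as an explanation for higher 25OHD going with more skin cancer (Anticancer properties).

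Diabetes and cancer are primary components, so the protocol itself names causes shared by achieved level and outcome.

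**2. Can a false threshold appear?** A simulation used 2,000,000 patients per scenario, with no effect of 25OHD or dose on events. Input from the protocol: 22% event risk. Assumed: mean achieved 25OHD of 45 versus 24 ng/ml, SD 10, and a prognostic factor correlated -0.2 to -0.4 with achieved 25OHD and carrying an event odds ratio of 1.35 to 2.46 per SD.

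| Comparison (true risk ratio 1.00) | Weakest confounding | Strongest confounding |
|---|---|---|
| High vs low dose, all randomized | 1.00 | 1.00 |
| 30 ng/ml or more vs less, arms pooled | 0.96 | 0.79 |
| 40 ng/ml or more vs less, high-dose arm | 0.93 | 0.67 |
| High vs low dose within 30 to 40 ng/ml | 1.10 | 1.62 |

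The level-based contrasts suggest protection and the within-stratum contrast suggests harm, although neither exists.

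**3. Timing of samples against events**, assuming a constant hazard and the planned risks of 22% and 13% at 2 years.
- Low-dose hazard: -ln(0.78)/2 = 0.1242 per year.
- Share of low-dose events before month 3: (1 - exp(-0.1242 × 0.25))/0.22 = 0.0306/0.22 = 14%.
- Share before month 12: (1 - exp(-0.1242))/0.22 = 0.1168/0.22 = 53%.
- High-dose hazard: -ln(0.87)/2 = 0.0696 per year; share before month 3: 0.0173/0.13 = 13%.
- With 291 evaluable per arm, expected events are 64.0 + 37.8 = 101.8. After month 3 there remain 64.0 × 0.86 + 37.8 × 0.87 = about 88.

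Month-3 values therefore precede most events; month-12 values precede fewer than half of those in the low-dose arm.

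**4. HbA1c.** Inputs from Study population and sample size: 6% de novo diabetes and a 33% reduction, so 6% × 0.67 = 4%. With 320 per arm this is about 19 versus 13 cases. Assumed: HbA1c SD 0.4, and correlation r of 0.5 to 0.8 between HbA1c and the glycaemia that defines diabetes.

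*No treatment effect on HbA1c, one third of diabetes prevented.* The cut points are t0 = 1.555 and t1 = 1.751, with normal densities 0.1191 and 0.0862.
- Diabetes-free subset: r × 0.4 × (0.1191/0.94 - 0.0862/0.96) = r × 0.4 × 0.037 = +0.007 to +0.012, against a truth of 0.
- Diabetes subset: r × 0.4 × (0.0862/0.04 - 0.1191/0.06) = r × 0.4 × 0.169 = +0.034 to +0.054. Simulation gave +0.035 to +0.054.

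*True shift of -0.08 in everyone* (which also yields 6% versus 4% diabetes). Simulation gave about -0.07 in the diabetes-free subset and -0.03 to -0.05 in the diabetes subset.

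**The case against.** The best defence is that the subgroup sentence is loose and labelled post hoc. It does not say that arms will be compared within achieved-level strata, nor which sample defines achieved, and an analysis plan that is not shown may add a landmark and adjustment. Neither the Objectives section nor the list of secondary parameters contains a threshold objective; the promise sits in a justification of the assay and in a perspectives paragraph. The authors plainly know the limits of observational data. All this lowers the weight of the point. It does not remove it, because the article itself lists achieved level as a subgroup variable and twice says the trial will find the level needed.

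On HbA1c, there is a sound reason for the split: values after diabetes onset reflect anti-diabetic drugs. Diabetes incidence is analysed separately as a primary component, so that benefit is not lost. The diabetes-free bias is small.

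A reader might draw three stronger conclusions that the documents do not support:
- *That achieved-level subgroup and arm nearly coincide.* No distribution is given for the low-dose arm. Under the assumptions in step 2, 27% of low-dose patients exceed 30 ng/ml, and the 30 to 40 stratum holds about 24% of the high-dose and 22% of the low-dose arm.
- *That the plan uses later samples to explain earlier events.* No section says so. The 53% figure is a warning about that choice, not a description of the plan.
- *That the HbA1c bias always runs towards no effect.* With a true benefit it shrinks the difference; with no HbA1c effect but fewer diabetes cases it creates a spurious positive one.

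**Conclusion.** The point holds in a limited form and is worth correcting. Achieved 25OHD does not belong among subgroups for the treatment effect, and the trial cannot determine a protective threshold in the sense that Patient follow-up and Conclusion and perspectives state. A labelled, adjusted exposure-response description remains legitimate. That conclusion rests on the text and needs no numerical assumption. The illustrative risk ratios (0.96 to 0.79 for a false threshold, 1.10 to 1.62 for false harm) depend on assumed 25OHD distributions and confounding and show only what is possible.

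The HbA1c point is secondary: about 0.01 points of bias in the diabetes-free subset, up to about 0.05 in a diabetes subset of only some 32 patients, and a direction that depends on the true effect. It also requires a treatment effect on diabetes, which the protocol assumes.

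Nobody should infer that the trial's main result is at risk. The intention-to-treat Cox comparison of the composite does not condition on achieved 25OHD or on HbA1c.

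**What to change.** 1. Remove achieved 25OHD from the subgroups used to examine the treatment effect.
2. Analyse it instead with a Cox model of first events after month 3, in patients still event-free then, using the month-3 value; or use a time-updated 25OHD value. Adjust for baseline risk factors and label the result observational.
3. Reword the threshold statements in Patient follow-up and Conclusion and perspectives as an exploratory aim: to describe the association between 25OHD level and later events.
4. Add a between-arm HbA1c comparison in all randomized patients, stating how values after the start of anti-diabetic treatment are handled. Keep the split by de novo DM as description.

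The cost is some wording and a few extra models; the 25OHD samples and HbA1c visits are already in Table 1. There are two drawbacks. The threshold aim becomes more modest, and all-patient HbA1c mixes values before and after anti-diabetic treatment, which can dilute an effect; hence the need to state the handling in advance.
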